### Overview of trial design

SARAH is a prospective, randomised open-label, multicentre trial comparing RE and sorafenib in patients with advanced HCC. In SARAH, the aim will be to recruit a minimum of 440 patients over a period of 24 months across 28 centres in France. Centres will be chosen based on their potential to recruit a high number of patients, and the expertise in intra-arterial treatment, and will receive special training with RE. Eligible patients will be stratified 1:1 to receive either systemic therapy with oral sorafenib (control arm) or RE with SIR-Spheres™ (RE arm; Figure 1).

**Figure 1 Fig1:**
[figure not shown]
**Overview of the SARAH trial design.** ECOG, Eastern Cooperative Oncology Group; RE, radioembolisation.

### Randomisation

Eligible patients will be randomised 1:1. The randomisation will be stratified by centre, Eastern Cooperative Oncology Group (ECOG) score (0 versus 1), the presence or absence of macroscopic vascular invasion seen on imaging (obstruction of the portal vein or its branches) and previous chemoembolisation failure. The list will be balanced by different sized blocks and randomly alternated. The data coordination centre will prepare the randomisation list before enrolment begins.

### Treatments

In the sorafenib arm, patients will receive oral treatment with sorafenib (400 mg twice daily) beginning in the week following randomisation (the first day of receiving treatment is defined as D0 in Table 2). Treatment suspensions and dose reductions (to 400 mg/d) will be permitted in case of adverse events (based on the SHARP study[6]) and at the treating practitioner’s discretion. Treatment may be resumed once the adverse events have been resolved, with incremental doses up to 400 mg twice daily.

**Table 2 Tab2:** **SARAH trial assessment schedule**

Visits	Enrolment/randomisation	D0	D15	M1	M2	M3	M4	M5	M6	M7	M8	M9	End of participation
Identification	X												
Verification of selection criteria	X												
Consent signature	X												
Initial assessment – history	X												
CT scan	X			X		X			X			X	X
CT perfusion	X			X		X			X				
Laboratory tests	X	X	X	X	X	X	X	X	X	X	X	X	X
Classification	X			X	X	X	X	X	X	X	X	X	X
Clinical examination				X	X	X	X	X	X	X	X	X	X
Quality of life questionnaires	X			X		X			X			X	X
Preparatory angiography		X											
Scintigraphy		X											
RE		X											
Start of sorafenib treatment		X											
Retreatment^*^				X	X	X	X	X	X	X	X	X	
Cancer progression monitoring				X	X	X	X	X	X	X	X	X	X
Sorafenib monitoring				X	X	X	X	X	X	X	X	X	X
Concomitant medication				X	X	X	X	X	X	X	X	X	X
Adverse events				X	X	X	X	X	X	X	X	X	X

^*^Timing of retreatment depends upon type of retreatment (see text). CT, computed tomography; D, day; M, month; RE, radioembolisation.

In the RE arm, patients randomised to RE will require a hepatic angiogram, and a liver-to-lung shunt pre-assessment with technetium-99 m (^99m^Tc)-marked human serum albumin in order to determine their suitability for the RE procedure. Accessory tumoural vascular branches and extrahepatic vascular branches will be embolised using thrombogenic coils or vascular plugs in order to isolate the arterial supply of the afferent vessel that vascularises the tumour. A catheter will then be placed in the afferent vessel that vascularises the tumour, and 150 to 180 MBq of ^99m^Tc-marked human serum albumin will be injected. The injection rate and catheter position will mimic the anticipated RE procedure. After the injection, the patient will have the pulmonary shunt evaluated using a dual-head gamma camera or single-photon emission computed tomography (SPECT)/computed tomography (CT). The prescribed activity of SIR-Spheres™ will then be calculated based on the patient’s body surface area and the percentage tumour involvement as described by Kennedy *et al*.[19]. Patients who would receive a dose in the lungs higher than 25 Gy based on the liver-to-lung shunt pre-assessment will not receive RE, but will remain in this study arm as part of the intention-to-treat group (ITT). Patients who are eligible for RE will commence treatment between the second and fifth week after randomisation with a single session of treatment (the day on which RE is administered is defined as D0 in Table 2). In patients with bilobar involvement, contralateral RE will be administered within 30 to 60 days. In order to avoid premature retreatment with RE of any lobe due to late tumour response, retreatment with RE will only be considered beyond 3 months from D0 in the absence of objective response or if there is significant progression on imaging (stable or progressor according to the response evaluation criteria in solid tumours (RECIST) or European Association for the Study of the Liver (EASL)) in the treated region (same tumour or new tumour). Retreatment with RE will also be considered beyond 6 weeks in the event of partial failure of the initial treatment due to an identified correctible cause or if an insufficient tumour dose was delivered.

### Trial assessments

The last enrolled patient will be followed up for 12 months after the start of treatment (D0). All other patients will be followed up until the final visit of the last enrolled patient. Patients will therefore be followed up for a maximum of 48 months and a minimum of 12 months following start of treatment. All patients will be assessed by the schedule summarised in Table 2. Treatment will be discontinued if the patient withdraws consent, if the treating physician deems it necessary for medical reasons or if a serious adverse event occurs - after discontinuation, patients should be assessed by CT as soon as possible to assess response to treatment.

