## Background

The prevalence and incidence of hepatocellular carcinoma (HCC) is highly variable in different regions of the world but the burden is predicted to increase in the coming years[1]. In developed countries, early diagnosis of HCC is possible in 30 to 60% of patients, and as a result, HCC is often diagnosed in the advanced stage of disease (stage C of the Barcelona Clinic Liver Cancer classification – that is, ECOG performance status 1 to 2, portal invasion or extrahepatic spread, and Child-Pugh A-B). Curative treatment (by surgical resection, liver transplantation or thermoablative treatment) is possible only in a limited proportion of these patients[2], and many cases of HCC progress to an advanced stage following locoregional treatment. In patients with untreated advanced HCC, the prognosis is poor, with a median survival time of approximately 5 to 7 months, although this varies depending on Child‒Pugh score[3–5].

The pivotal Sorafenib Hepatocellular carcinoma Assessment Randomized Protocol (SHARP) trial showed that sorafenib (Nexavar™, Bayer HealthCare Pharmaceuticals, Berlin, Germany) treatment significantly increased median overall survival (OS) time by approximately 3 months versus placebo (10.7 months versus 7.9 months, respectively; *P* <0.001) in patients with advanced HCC[6]. These findings were subsequently confirmed in a randomised controlled trial in the Asia-Pacific, which showed OS of 6.5 months in the sorafenib arm versus 4.2 in the placebo arm (*P* <0.014)[7]. As a result of these data, sorafenib is the current recommended first-line treatment for advanced (Barcelona stage C) HCC[2]. However, while sorafenib increased OS in the SHARP study, it did not improve median time to symptomatic progression, and was associated with an overall adverse‒effect incidence of 80%. Adverse events experienced by >5% of patients in the SHARP trial included diarrhoea (13.1%), asthenia (7.4%), hand-foot skin reaction (7.0%), and erythema or desquamation (5.4%); dose reductions and treatment interruptions due to adverse effects occurred in 26% and 44% of cases, respectively[6]. As such, there is a medical need for the study of alternative treatment options for advanced HCC.

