### Outcome definitions

 OS is defined as the time from the date of randomisation to death from any cause. PFS - the time from the date of first treatment to disease progression - and tumour response rate (complete response, partial response, stability, or progression) will be determined from serial CT scans using RECIST, modified RECIST, EASL criteria for HCC, and Choi criteria[21]. Radiological examinations will be conducted by abdominal radiologists at each centre followed by a separate centralised review of radiological examinations. The general and liver disease-specific quality of life scores will be calculated using the European Organisation for Research and Treatment of Cancer (EORTC) quality of life questionnaire (QLQ-C30) version 3 and the HCC-specific QLQ-HCC 18 questionnaire[22]. Adverse events will be reported according to National Cancer Institute criteria (National Cancer Institute Common Terminology criteria for Adverse Events (NCI CTCAE) Version 4.0)[23].

The cost of therapy from the hospital’s perspective will be estimated by including all the resources that are directly attributable to the procedure (that is, equipment, tests, total work time, and so on), which will be assigned a value based on the purchase price by the hospital. The mean overall cost per patient from the payer’s perspective will include the relative stay index and readmissions during the patient’s follow-up period. Calculation of the incremental cost-effectiveness ratio per year of survival or the incremental cost-utility ratio between RE and sorafenib will be complemented by the bootstrap resampling method and an acceptability curve for the cost-effectiveness ratio.

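### The CT triggered by stopping treatment will be done more often on sorafenib than on RE, which can modestly bias time-to-event PFS towards RE

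*Protocol article*

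**What the plan says.** Trial assessments puts both arms on one schedule: "All patients will be assessed by the schedule summarised in Table 2". In Table 2 the CTs fall at enrolment, M1, M3, M6, M9 and end of participation, and the visits count from D0. The same section gives the grounds for stopping: "Treatment will be discontinued if the patient withdraws consent, if the treating physician deems it necessary for medical reasons or if a serious adverse event". It then adds the unscheduled scan: "after discontinuation, patients should be assessed by CT as soon as possible to assess response to treatment". No arm is named.

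Under Treatments, sorafenib is taken by mouth twice daily, and it may be suspended, reduced and resumed. RE begins "with a single session of treatment" on D0, but more can follow: "In patients with bilobar involvement, contralateral RE will be administered within 30 to 60 days". Retreatment may be considered beyond 6 weeks or beyond 3 months, depending on the reason, and Table 2 lists retreatment from M1 to M9.

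Under Outcome definitions, PFS runs from first treatment to progression, and PFS and response "will be determined from serial CT scans using RECIST, modified RECIST, EASL criteria for HCC, and Choi criteria". PFS at 6 months is a secondary endpoint. Statistical analysis also plans Kaplan-Meier curves and median times for PFS. The Discussion presents a blind imaging review as the safeguard against bias in PFS.

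**The concern.** Progression is dated by the scan that shows it, so the recorded date depends on when scans are done. Between M3 and M6 there are three months without a scheduled CT. A sorafenib patient who has progressed and stops in month 4 is scanned then. An RE patient with the same course, and no treatment under way to stop, is scanned at M6. If the extra scan is commoner in one arm, that arm's progressions are recorded earlier even when the true times are equal. Blind reading does not help, because the arms differ in when images exist, not in how they are read.

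At stake are the PFS curve, the median PFS and the PFS comparison, all secondary. The primary endpoint, OS, does not depend on scans.

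**Working it through.** **The plan's own figures.** The plan gives no number on this point. Its 400 patients rest on OS and are not affected (Freedman: 281 events / 0.710 mean event probability = 396).

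**Inputs from the documents.** CT at M1, M3, M6 and M9 in both arms; extra CT after discontinuation; PFS dated from CT.

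**Assumed inputs.** Exponential progression, identical in both arms, with median 3.5, 5 or 7 months. Scans within 1 week of their date. Extra CT 0-0.5 month after stopping, on sorafenib only (the worst case). Stopping either unrelated to progression (30-50% by 6 months) or linked to it (half of progressors stop within a month).

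**Step 1: PFS at 6 months with the M6 CT counted.** Everyone who has progressed by M6 is found by M6, with or without an earlier scan. Both arms then show the true value S(6) = 0.5^(6/median), and the expected difference is zero. Simulation gives 0.5 percentage points or less, which is noise.

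**Step 2: the same endpoint cut at exactly 6.0 months.** About half of the M6 scans now fall after the cut.
- RE shows about [S(3) + S(6)] / 2.
- On sorafenib, half of the progressors not yet seen stop within a month. The mean delay from progression to CT is 0.5 + 0.25 = 0.75 month. With progression spread evenly over the 3-month gap, about 1 - 0.75/3 = 0.75 of them are scanned before the cut.
- The sorafenib figure is therefore lower by 0.5 × [S(3) - S(6)] × 0.5 × 0.75.

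| True median (months) | S(3) | S(6) | RE at 6.0 | Reduction | Sorafenib at 6.0 | Simulated, RE vs sorafenib |
|---|---|---|---|---|---|---|
| 3.5 | 0.552 | 0.305 | 0.428 | 0.046 | 0.382 | 43% vs 38% |
| 5 | 0.660 | 0.435 | 0.548 | 0.042 | 0.505 | 55% vs 51% |
| 7 | 0.743 | 0.552 | 0.648 | 0.036 | 0.612 | 65% vs 61% |

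The gap of about 4 to 5 points thus needs both an exact cut and linked stopping. With unrelated stopping it is about 1 point.

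**Step 3: the PFS curve.** In simulation on the same assumptions (200,000 per arm), the Cox hazard ratio to 9.5 months, RE versus sorafenib, is:
- 0.98-1.00 with unrelated stopping;
- 0.93-0.96 with linked stopping.

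Medians can shift more, because the curve falls in steps at sparse visits. In one run with true median 3.5 months and linked stopping they were 5.86 and 4.97 months, a gap of 0.89 month.

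**Step 4: sensitivity.** A second simulation used 200 per arm, 400 runs and true medians of 4 and 6 months. Every scheduled scan fell exactly on its date, with CTs every 3 months after M9 (assumed). Its log-rank hazard ratios are inverted here to RE versus sorafenib.

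| Sorafenib patients with a linked extra CT | Sorafenib vs RE | RE vs sorafenib | Two-sided rejection at nominal 5% |
|---|---|---|---|
| 10% | 1.02-1.04 | 0.96-0.98 | 5-6% |
| 20% | 1.05-1.07 | 0.93-0.95 | 9-10% |
| 40% | 1.10-1.14 | 0.88-0.91 | 13-19% |

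Unrelated stopping at 10-40% gave 1.00-1.03 with rejection of about 4-6%. Giving 10% of RE patients a linked extra CT as well reduced the 40% row to 1.08-1.10. The shifts exceed those in Step 3 because scans exactly on their dates tie most events at the visits. Spreading scans over a 1-week window weakens the effect.

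**The case against.** **RE can also be discontinued.** This stands. Contralateral sessions and retreatment are provided for, so a reader who infers from "with a single session of treatment" that the extra CT can occur only on sorafenib goes beyond the text. The asymmetry is one of frequency. It remains, because the contralateral session applies to bilobar disease and is due by day 60, and retreatment is a separate decision, not a running course. Retreatment decisions depend on imaging and might prompt extra RE scans. That would act the other way, and the documents do not allow it to be sized.

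**Progression is not a listed reason for stopping.** Correct, and without a link the bias is negligible. But medical reasons are left to the treating physician in an open-label trial with monthly progression monitoring, so some link is plausible. The assumption that half of progressors stop within a month has no source in the documents.

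**The M6 CT protects PFS at 6 months.** This stands if that scan is counted. A reader might infer a bias of several points in this endpoint, but the article does not say that the estimate is cut at exactly 6.0 months. The M6 CT does not protect the curve or the medians.

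**The Background seems to give a discontinuation rate.** It does not. It reports of the earlier sorafenib trial that "dose reductions and treatment interruptions due to adverse effects occurred in 26% and 44% of cases, respectively". Those are reductions and interruptions, and this trial allows treatment to resume. They cannot stand in for permanent discontinuation.

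**Dating rules belong in the analysis plan.** Agreed, and their absence from an article is no fault. The point is the effect of a scan rule and a PFS analysis that the article does state, with a safeguard that does not reach it.

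**Conclusion.** The point holds in a limited form. The discontinuation CT will be more frequent on sorafenib, and the resulting shift in time-to-event PFS, if any, favours RE. With equal true PFS the apparent hazard ratio is about 0.98-1.00 if stopping is unrelated to progression and about 0.93-0.96 if half of progressors stop within a month. The most extreme case tried, with 40% linked stopping and no spread in visit dates, reaches 1/1.14 = 0.88. All of these sizes rest on assumed discontinuation rates and assumed PFS.

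The documents do not support three stronger readings: that the extra scan is confined to sorafenib, that bias is certain, or that PFS at 6 months is necessarily distorted. OS, the primary endpoint, is unaffected. This is a modest, cheaply removed weakness in a secondary analysis.

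**What to change.** Leave the discontinuation CT in place for care and for response, and change only how PFS is analysed:

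1. Define PFS at 6 months as status at the M6 CT with its visit window, so that the common scan is counted in both arms.
2. Analyse the PFS curve as interval-censored, at least as a planned sensitivity analysis. Up to M9, set the interval limits by the scheduled CTs, because limits set by a scan that progression itself may have prompted would bring the imbalance back.
3. As a simpler alternative to item 2, date a progression first seen on an unscheduled CT to the next scheduled CT, up to M9 only. Table 2 has no scheduled CT between M9 and end of participation, so the rule would shift later events too far.

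No sentence is needed to say that scheduled CTs apply to everyone, since Trial assessments already puts all patients on Table 2. In the Discussion, confine the claim for blind review to bias in reading images.

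Cost: a few sentences, one extra analysis and slightly coarser PFS dates. No new scans and no change to treatment rules.

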### Outcome measures

The primary endpoint of the SARAH trial is OS. Secondary endpoints include: adverse events rate, progression-free survival (PFS) at 6 months according to RECIST[20], modified RECIST, EASL and Choi criteria; tumour response rate; general or liver disease-specific QoL scores; and cost of each strategy.

Cost endpoints are: the cost of RE from the hospital perspective; the average cost per patient from the payer’s perspective; and the incremental cost-effectiveness or cost-utility ratio.

### Outcome definitions

 OS is defined as the time from the date of randomisation to death from any cause. PFS - the time from the date of first treatment to disease progression - and tumour response rate (complete response, partial response, stability, or progression) will be determined from serial CT scans using RECIST, modified RECIST, EASL criteria for HCC, and Choi criteria[21]. Radiological examinations will be conducted by abdominal radiologists at each centre followed by a separate centralised review of radiological examinations. The general and liver disease-specific quality of life scores will be calculated using the European Organisation for Research and Treatment of Cancer (EORTC) quality of life questionnaire (QLQ-C30) version 3 and the HCC-specific QLQ-HCC 18 questionnaire[22]. Adverse events will be reported according to National Cancer Institute criteria (National Cancer Institute Common Terminology criteria for Adverse Events (NCI CTCAE) Version 4.0)[23].

The cost of therapy from the hospital’s perspective will be estimated by including all the resources that are directly attributable to the procedure (that is, equipment, tests, total work time, and so on), which will be assigned a value based on the purchase price by the hospital. The mean overall cost per patient from the payer’s perspective will include the relative stay index and readmissions during the patient’s follow-up period. Calculation of the incremental cost-effectiveness ratio per year of survival or the incremental cost-utility ratio between RE and sorafenib will be complemented by the bootstrap resampling method and an acceptability curve for the cost-effectiveness ratio.

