### Statistical analysis

Results will be reported according to the Consolidated Standards of Reporting Trials (CONSORT) statement. An ITT analysis will be performed, keeping patients in their randomisation group and including protocol deviations. A ‘per-protocol’ sensitivity analysis will also be performed. A study flowchart will be provided, including the number of patients who: are eligible; are randomised to receive treatment; are followed up; withdraw from the study; and are lost to follow-up. Major protocol deviations and the reasons for withdrawal from the study will be described.

The Kaplan and Meier method will be used to calculate survival (OS and PFS). The comparison of survival rates at 12 months between the two treatment groups will be performed using the log rank test (Mantel-Haenszel version). In addition, the treatment effect, once adjusted for the stratified randomisation factors, will be calculated via: (1) a stratified log rank analysis; and (2) a Cox’s regression model.

The median survival times (OS and PFS) in both treatment groups will be calculated, along with the confidence interval associated with the difference or with the median survival time ratio[24].

Toxicity will be reported according to NCI CTCAE Version 3.0, with particular reference to the proportion of patients experiencing grade 3/4 toxicity in each treatment arm.

The objective response will be determined via the RECIST and modified (m)RECIST criteria, the EASL criteria for HCC, and the Choi criteria, and a comparison will be made between the two treatment groups using the ‘best response during follow-up’ criterion. The response rates will be calculated by comparing the number of patients who responded during follow-up (complete or partial response) with the total number of randomised patients in each group. The related confidence intervals will be calculated and compared between the two groups using Pearson’s chi-squared test.

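### PFS is defined from first treatment to progression: the clock starts at different times in the two arms, never starts for untreated patients, and death is not named as an event

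*Protocol article*

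**What the plan says.** Under Outcome definitions in the protocol article, two neighbouring time-to-event definitions differ in both start and event:

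- OS: "OS is defined as the time from the date of randomisation to death from any cause".
- PFS: "PFS - the time from the date of first treatment to disease progression", determined from serial CT scans.

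Outcome measures lists "progression-free survival (PFS) at 6 months according to RECIST" and three further criteria among the secondary endpoints.

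The Treatments section sets the start of treatment by arm. Sorafenib is given "beginning in the week following randomisation". For RE, "Patients who are eligible for RE will commence treatment between the second and fifth week after randomisation", and D0 is the day RE is administered. RE patients whose predicted lung dose exceeds 25 Gy "will not receive RE, but will remain in this study arm as part of the intention-to-treat group (ITT").

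Statistical analysis states: "An ITT analysis will be performed, keeping patients in their randomisation group and including protocol deviations". It applies the Kaplan-Meier method to both OS and PFS.

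No section gives a PFS start date for patients who are never treated, and none adds death as a PFS event.

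**The concern.** There are three defects in one definition.

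1. **Start.** Time zero comes after randomisation and depends on the arm. RE patients must survive and stay treatable through a longer wait before their clock starts.
2. **Population.** The protocol itself creates a group that is randomised to RE, not given RE, and kept for ITT. Under the PFS definition these patients have no time zero. The stated ITT analysis therefore cannot be carried out for this endpoint. Response rates, by contrast, are to be calculated over all randomised patients, so the two imaging endpoints would rest on different populations.
3. **Event.** With progression as the only event, a patient who dies without documented progression does not fail. That quantity is time to progression. Reported as PFS, it would carry a name that its definition does not meet.

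At stake is a randomised comparison of 6-month PFS and median PFS that readers will take as ITT and as including deaths.

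**Working it through.** **Plan's own figure.** No figure is stated for PFS. The 400 patients rest on OS and reproduce. With medians of 10.7 and 15 months, HR = 10.7/15 = 0.713. The Schoenfeld formula at two-sided 5% and 80% power gives 276 events. With uniform accrual over 24 months plus 12 months of follow-up, the event probabilities are 0.767 (sorafenib) and 0.653 (RE), mean 0.710, so N = 276/0.710 = 389. Freedman's formula gives 281 events and N = 396. Both are within 3% of 400. OS already runs from randomisation, so none of this changes.

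**Gap between clocks** (Treatments section). Sorafenib starts on about days 1-7, RE on about days 8-35.
- Smallest gap: 8 − 7 = 1 day.
- Largest gap: 35 − 1 = 34 days.

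**Deaths by the 6-month time point** (OS medians from the sample size section, exponential survival). Proportion dead = 1 − exp(−ln2 × t/median).
- Sorafenib: 1 − exp(−0.693 × 6/10.7) = 32.2%.
- RE: 1 − exp(−0.693 × 6/15) = 24.2%.

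These are all deaths, with or without earlier progression. They show that the handling of death is not a marginal matter at 6 months.

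**RE patients who die before D0** (RE median 15 months, 30.44 days per month).
- 2 weeks (0.460 months): 1 − exp(−0.693 × 0.460/15) = 2.1%.
- 5 weeks (1.150 months): 1 − exp(−0.693 × 1.150/15) = 5.2%.

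Of 200 patients that is about 4 to 10 with no PFS time. A treatment start as early as day 8 gives 1.2%.

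**Effect of censoring deaths.** The documents give no PFS rate. Assumptions: exponential PFS with median 4-6 months, and a share s of 15-35% of PFS events being deaths without progression. True 6-month PFS is S = exp(−0.693 × 6/median); with deaths censored it becomes S^(1−s).

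| Median PFS | True S(6) | s = 15% | s = 25% | s = 35% |
|---|---|---|---|---|
| 4 months | 35.4% | 41.3% | 45.9% | 50.9% |
| 5 months | 43.5% | 49.3% | 53.6% | 58.2% |
| 6 months | 50.0% | 55.5% | 59.5% | 63.7% |

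The rise runs from 5.5 points (median 6, s = 15%) to 15.5 points (median 4, s = 35%).

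**Effect of dropping untreated RE patients.** Assumptions: 10% of the RE arm untreated, with median PFS 2-3 months, so that their 6-month PFS is Su = 12.5% or 25.0%. If S is the rate in the whole arm, the treated 90% have (S − 0.1 Su)/0.9, a rise of (S − Su)/9.
- Smallest: (35.4 − 25.0)/9 = 1.2 points.
- Largest: (50.0 − 12.5)/9 = 4.2 points.

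If S is instead the rate in treated patients only, the rise is 0.1 × (S − Su), or 1.0 to 3.8 points. Either way it is about 1 to 4 points.

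**The case against.** **Shorthand.** The endpoint is called progression-free survival and is grouped with OS as survival in Statistical analysis. In a condensed article, leaving out death may be shorthand, and no section says that deaths are censored. This stands as a caution: death may have been intended. But the definition is stated, it stands next to an OS definition that does name death, it is tied to CT scans, and nothing corrects it. If death was intended, the sentence is still wrong as written.

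**Secondary endpoint.** PFS is secondary. OS was chosen as primary partly because imaging progression behaves differently in the two arms. This stands and limits the severity.

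**Blinded imaging review.** The Discussion offers it as protection against bias in PFS. It protects the reading of scans, not the start date, the population or the event.

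**Stronger readings that the documents do not support.**
- *The definition favours RE.* Dropping untreated RE patients would flatter RE. A later RE clock, however, shortens measured RE time for a given progression date. Table 2 shows CT at enrolment and next at M1, with none at D0, so progression during the wait in patients who go on to treatment is found later and charged to the shorter clock. The net direction is not established.
- *Only RE patients lose their clock.* A sorafenib patient who never starts loses it too. The protocol makes this likelier in RE, not exclusive to it.
- *Early RE deaths follow the control hazard.* The 10.7-month median would give 2.9% to 7.2% before D0, but the protocol's figure for RE is 15 months. Even 2.1% to 5.2% is probably too high, since entry requires life expectancy above 3 months.
- *The 6-month rate should be read at about 7 months, or PFS cut at M9.* An RE patient treated at week 5 has the M6 scan at 6 + 1.15 = 7.15 months from randomisation, after 7 months. The long CT interval after M9 does not bear on a 6-month rate, and a cut there could prevent estimation of the planned median PFS.

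**Conclusion.** The definition is wrong as written and should be fixed. Taken literally, it gives an endpoint that is not PFS, is not measured from a common origin, and cannot be analysed in the ITT population that the protocol promises. These three conclusions follow from the text alone.

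The sizes are less firm. The 1-34 day gap comes from the protocol's own windows. The 32% and 24% deaths by 6 months, and the 2.1-5.2% of RE deaths before D0, rest on the protocol's OS medians and constant hazards. The 5-16 points from censoring deaths and the 1-4 points from dropping untreated RE patients rest on assumed PFS medians, death shares and untreated proportions, and illustrate scale only. The 5-16 points are an inflation within an arm, not a between-arm bias; that bias is of uncertain direction. The primary analysis of OS and the sample size are unaffected.

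**What to change.** - Define PFS as the time from randomisation to first documented progression or death from any cause, whichever comes first, in all randomised patients.
- If the quantity now defined is wanted, report it as time to progression.
- Use first treatment as time zero only in a sensitivity analysis.
- Table 2 schedules scans from D0, so RE scans will fall later on a clock that starts at randomisation. Add a sensitivity analysis for this, for example one that treats progression as interval-censored between scans.

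The cost is a wording change and one or two added analyses. Randomisation and death dates are already needed for OS, and the trial was still recruiting when the article appeared. The downside is that reported PFS will be somewhat shorter.
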